# Deep Brain Stimulation for Tremor Tractographic Versus Traditional (DISTINCT): Study Protocol of a Randomized Controlled Feasibility Trial

**DOI:** 10.2196/resprot.6885

**Published:** 2016-12-22

**Keywords:** deep brain stimulation, essential tremor, magnetic resonance tractographic-assisted implantation

## Abstract

**Background:**

Essential tremor is a movement disorder that can result in profound disability affecting the quality of life. Medically refractory essential tremor can be successfully reduced by deep brain stimulation (DBS) traditionally targeting the thalamic ventral intermediate nucleus (Vim). Although this structure can be identified with magnetic resonance (MR) imaging nowadays, Vim-DBS electrodes are still implanted in the awake patient with intraoperative tremor testing to achieve satisfactory tremor control. This can be attributed to the fact that the more effective target of DBS seems to be the stimulation of fiber tracts rather than subcortical nuclei like the Vim. There is evidence that current coverage of the dentatorubrothalamic tract (DRT) results in good tremor control in Vim-DBS. Diffusion tensor MR imaging (DTI) tractography-assisted stereotactic surgery targeting the DRT would therefore not rely on multiple trajectories and intraoperative tremor testing in the awake patient, bearing the potential of more patient comfort and reduced operation-related risks. This is the first randomized controlled trial comparing DTI tractography-assisted stereotactic surgery targeting the DRT in general anesthesia with stereotactic surgery of thalamic/subthalamic region as conventionally used.

**Objective:**

This clinical pilot trial aims at demonstrating safety of DTI tractography-assisted stereotactic surgery in general anesthesia and proving its equality compared to conventional stereotactic surgery with intraoperative testing in the awake patient.

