This clinical pilot trial, Deep Brain Stimulation for Tremor Tractographic Versus Traditional (DISTINCT), in patients with medically refractory essential tremor aims at demonstrating safety of DTI tractography-assisted stereotactic surgery in general anesthesia and proving its equality compared to conventional AC-PC coordinate-based stereotactic surgery with intraoperative testing in the awake patient. Accordingly, a randomized, controlled, rater-blinded, parallel group study was set up involving 2 patient groups each assigned to 1 of the aforementioned treatments. Established assessments of tremor and quality of life are used to compare the effect of treatments, which is then related to effective electrode contact positions.

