### Secondary Objectives

To assess the effect in tremor reduction of both interventions at 6 months based on the total power in tremor analysisTo assess the quality of lifeTo assess the optimal electrode contact positionTo assess differences in duration of neurosurgery in both groupsPsychiatric assessmentTo assess safety of interventionTo show equality of both interventions in tremor reduction at 6 months based on the total power in tremor analysis

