### Biostatistical Planning and Analysis

#### Sample Size Calculation

This is a feasibility study in 24 patients with essential tremor (12 DTI tractography-assisted implantations, 12 implantations with conventional intraoperative testing). To obtain estimates for the treatment effect and its variance and, thus, to obtain a solid basis for the sample size calculation of the subsequent confirmative trial, the FTMTRS score at 6 months after intervention and its change from baseline will be subjected to exploratory descriptive analysis. Julious [20] found that a sample size of 12 per group in pilot studies seems reasonable for generation of pilot data. Given a continuous outcome, increasing the sample size beyond 12 per group did not have profound influence on the confidence interval. A dropout rate of 25% is assumed, so 30 patients will be assessed for eligibility.

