#### Analysis of the Primary Endpoint

The primary efficacy analysis of this clinical trial will be conducted according to the intention-to-treat principle (ITT). This means that the patients will be analyzed in the treatment arms to which they were randomized, irrespective of whether they refused or discontinued the treatment or whether other protocol violations are revealed. Confidence intervals (95%) will be calculated for means and standard deviations within groups as well as for the difference between groups in the ITT population. The effects of DTI tractography-assisted versus conventional intraoperative testing with respect to the FTMTRS score at 6 months will be estimated and tested within a linear regression model including treatment and the baseline FTMTRS score as covariates. A conservative estimate of the effect size anticipated for a subsequent confirmative trial will be derived from these analyses by a combination of clinical and statistical judgement.

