## Discussion

The DISTINCT trial is an investigator-initiated, randomized, controlled, observer-blinded trial comparing DTI tractography-assisted stereotactic surgery with a target point of the DRT in general anesthesia to stereotactic surgery of the thalamic/subthalamic region as conventionally used. It is hypothesized that DTI tractography-assisted stereotactic surgery in general anesthesia is safe and is equal to conventional AC-PC coordinate-based stereotactic surgery with intraoperative testing in the awake patient.

To examine the 2 discrete treatment groups, a randomized controlled parallel group study is the appropriate design. Efforts to blind patients would annihilate favorable effects in the tractography-based treatment group (single trajectory, shorter duration of surgery), so a rater-blinded design is implemented. Reliability is enhanced by double rating of video-documented tremor assessments by 2 independent raters.

Chen et al [15] retrospectively analyzed a series of AC-PC coordinate-based Vim-DBS implantations in general anesthesia and compared it to implantations in awake patients. As clinical outcome parameter, a self-evaluation with a mailed questionnaire was used which led to a variable follow-up latency and a considerable drop-out rate. As a contrast, the focus of our study is the DTI tractography-assisted Vim-DBS implantation. Furthermore, by means of a randomized controlled trial and clinical tremor assessment more valid data can be yielded.

DTI tractography of the DRT can generally be achieved with probabilistic [21] or deterministic [10,11] fiber tracking; however, only the latter is available for stereotactic planning in CE-approved planning systems. As a result, this study employs deterministic fiber tracking.

Tractography with a seed ROI in the ipsilateral dentate nucleus and target ROI in the ipsilateral precentral gyrus reliably yields the nondecussating fibers of the DRT described by Meola et al [22]. However, as the decussating fibers cross below the level of the red nucleus and converge with the nondecussating fibers before entering the thalamus, the issue of decussation has little relevance to the stimulation target site in the subthalamic region.

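### The article sets out to prove equality and demonstrate safety, but an exploratory difference analysis with no margin in 12 patients per arm can only estimate the difference and describe event rates

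*Protocol article*

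**What the plan says.** Equality is claimed in four places in the protocol article.

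- Abstract, Objective: the trial aims at "proving its equality compared to conventional stereotactic surgery with intraoperative testing in the awake patient".
- Introduction: it "aims at demonstrating safety of DTI tractography-assisted stereotactic surgery in general anesthesia and proving its equality".
- Secondary Objectives: one item is to "show equality of both interventions in tremor reduction at 6 months based on the total power in tremor analysis".
- Discussion: the hypothesis is that the tractography-assisted method "is safe and is equal to conventional AC-PC coordinate-based stereotactic surgery with intraoperative testing in the awake patient".

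The statistical sections describe something else.

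- Sample Size Calculation: a feasibility study with "12 DTI tractography-assisted implantations, 12 implantations with conventional intraoperative testing", sized by a rule of thumb for pilot studies. The 6-month tremor score and its change from baseline "will be subjected to exploratory descriptive analysis", in order to plan a later confirmative trial.
- Analysis of the Primary Endpoint: 95% confidence intervals are given within groups and for the between-group difference, and the treatment effects "will be estimated and tested within a linear regression model including treatment and the baseline FTMTRS score as covariates".
- Analysis of Secondary Endpoints: total power, the endpoint of the equality objective, is handled like the primary endpoint. All secondary analyses are exploratory. Adverse event and serious adverse event rates are reported as treated, with two-sided 95% intervals.

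No equivalence or non-inferiority margin appears, and no criterion for calling the methods equal or the new one safe.

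**The concern.** A test whose null hypothesis is no difference can give evidence of a difference. Failing to reject it does not show that the difference is small. Proving or showing equality needs a margin, and an interval narrow enough to fit inside it. The article makes the claim without the margin, and 12 per arm gives wide intervals. The stated aim and the stated method therefore conflict, and the conflict decides what the final report may conclude. If it stays, a non-significant comparison could be presented as meeting the aim while the data remain compatible with a sizeable disadvantage for implantation under general anesthesia.

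This is not a detail that an analysis plan could settle. A margin supplied later would be tested on the same 24 patients, and with that number only a wide margin has a reasonable chance of being met.

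**Working it through.** **Inputs from the article.** 12 patients per arm, 1:1 randomization, linear regression with treatment and baseline score, 95% intervals, safety described by event rates with two-sided 95% intervals.

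**Assumptions, because the article gives no figure.** Two-sided test level 0.05. Results are in units of the outcome SD, as no SD for the tremor score is stated. Correlation ρ between baseline and outcome of 0 (unadjusted), 0.5 or 0.7. Equivalence margins of 0.5 and 1.0 SD, for illustration only.

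**The plan's own figure.** The 12 per arm comes from a pilot-study rule with no power, effect size, SD or margin, so no power formula can reproduce it. The 30 patients to be assessed follow as 24 × 1.25 = 30. Neither number was derived from an equality criterion.

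**1. Precision.** Half-width of the 95% interval for the difference = t(0.975, df) × √(2/12) × √(1 − ρ²), with df = 22 unadjusted and 21 with the baseline covariate.

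- ρ = 0: 2.074 × 0.408 = 0.85 SD
- ρ = 0.5: 2.080 × 0.408 × 0.866 = 0.74 SD
- ρ = 0.7: 2.080 × 0.408 × 0.714 = 0.61 SD

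**2. Chance of p>0.05 when the arms truly differ by d SD.** Noncentral t with noncentrality d / [√(2/12) × √(1 − ρ²)].

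| True difference | ρ = 0 | ρ = 0.5 | ρ = 0.7 |
|---|---|---|---|
| 0.5 SD | 78% | 73% | 63% |
| 0.8 SD | 53% | 42% | 26% |
| 1.0 SD | 35% | 23% | 10% |

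**3. Power of a formal equivalence test.** Two one-sided tests at 5% each, which is the same as requiring the 90% interval to lie inside the margin, with truly equal arms.

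| Margin | ρ = 0 | ρ = 0.5 | ρ = 0.7 |
|---|---|---|---|
| 0.5 SD | 0.2% | 1.3% | 9% |
| 1.0 SD | 53% | 72% | 91% |

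For scale, the normal approximation n = 2 × [(z(0.95) + z(0.90)) / margin]² = 2 × [(1.645 + 1.282) / margin]² gives, for 80% power without adjustment, 69 per arm at 0.5 SD and 18 per arm at 1.0 SD.

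**4. Safety.** With 0 events in 12, the exact two-sided 95% upper limit is 1 − 0.025^(1/12) = 26.5%. With 1 in 12 the interval runs from 0.2% to 38.5%. An event with a true rate of 5% would be absent from 12 patients with probability 0.95^12 = 54%.

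**The case against.** The strongest reply is that the article already limits itself. It is titled a feasibility trial and calls itself a pilot. In the Abstract (Methods) and under Design, the primary objective is worded neutrally, as assessing or comparing tremor reduction. The secondary objectives list safety only as something to assess. All secondary analyses are exploratory, a confirmative trial is foreseen, and the Discussion concedes limited validity. The right tools, an interval for the difference and intervals for event rates, are already planned. All of this stands. It justifies 24 patients for estimation and means the analysis itself need not change. It does not justify the words prove and show, which sit in the aim, the hypothesis and a listed objective.

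Three stronger readings are tempting, and the documents do not support them.

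- A reader might infer that the trial will treat p>0.05 as equality. No section states such a rule. The risk is that a result could be misread, not that it would be.
- A reader might infer that a clearly worse method would most likely go undetected. That depends on the size of the deficit and on the baseline adjustment. At 0.8 SD the chance of missing it is 53% unadjusted, but 42% or 26% under the planned model with the assumed correlations.
- A reader might infer that safety is to be judged by the difference test. It is not; event rates with intervals are used. The safety concern is about precision and the absence of a criterion.

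Whether any margin in SD units is clinically acceptable cannot be judged from the article, so the equivalence figures show scale only.

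**Conclusion.** The concern holds as a mismatch between aim and method. The article claims that equality will be proved or shown, while the design offers an exploratory estimate and test of a difference, with no margin, in 12 patients per arm. That design cannot establish equality. A margin added later would not rescue the claim unless it were wide: at 0.5 SD the equivalence test almost never succeeds even with identical arms (0.2% to 9%), and reasonable power appears only around 1.0 SD and with a useful baseline correlation. Safety can be described but not demonstrated, since an event-free arm of 12 leaves rates up to 26.5% unexcluded.

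The half-widths (0.61 to 0.85 SD) rest on 12 analysed patients per arm and on the assumed correlations. The safety limit needs neither an SD nor a correlation. The sample size and the analysis model are suitable for a pilot and are not faulted here.

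**What to change.** - In the Abstract objective, the Introduction, the secondary objective on total power and the Discussion hypothesis, replace the equality claim with estimating the between-group difference and its 95% confidence interval. Replace the claim of demonstrating safety with describing adverse event rates and their 95% intervals.
- State that a p-value above 0.05 will not be interpreted as equality.
- Report the expected half-width of the interval for the difference, with the assumed baseline correlation.
- Leave any equivalence or non-inferiority claim to the confirmative trial, with a clinically justified margin and an interval level that matches the test (90% for two one-sided 5% tests, 95% for two one-sided 2.5% tests). A margin should not be added to this trial to rescue the wording: at 0.5 SD, for example, it could almost never be met.

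The cost is a change of wording in the protocol and, if one exists, the analysis plan. No patients, visits or analyses are added. The trial claims less, but what it claims is what its data can support.

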**Methods:**

The Deep Brain Stimulation for Tremor Tractographic Versus Traditional (DISTINCT) trial is a single-center investigator-initiated, randomized, controlled, observer-blinded trial. A total of 24 patients with medically refractory essential tremor will be randomized to either DTI tractography-assisted stereotactic surgery targeting the DRT in general anesthesia or stereotactic surgery of the thalamic/subthalamic region as conventionally used. The primary objective is to assess the tremor reduction, obtained by the Fahn-Tolosa-Marin Tremor Rating Scale in the 2 treatment groups. Secondary objectives include (among others) assessing the quality of life, optimal electrode contact positions, and safety of the intervention. The study protocol has been approved by the independent ethics committee of the University of Freiburg.

**Results:**

Recruitment to the DISTINCT trial opened in September 2015 and is expected to close in June 2017. At the time of manuscript submission the trial is open to recruitment.

**Conclusions:**

The DISTINCT trial is the first to compare DTI tractography-assisted stereotactic surgery with target point of the DRT in general anesthesia to stereotactic surgery of the thalamic/subthalamic region as conventionally used. It can serve as a cornerstone for the evolving technique of DTI tractography-assisted stereotactic surgery.

**ClinicalTrial:**

ClinicalTrials.gov NCT02491554; https://clinicaltrials.gov/ct2/show/NCT02491554 (Archived by WebCite at http://www.webcitation.org/6mezLnB9D). German Clinical Trials Register DRKS00008913; http://drks-neu.uniklinik-freiburg.de/drks_web/navigate.do?navigationId=trial.HTML&TRIAL_ID=DRKS00008913 (Archived by WebCite at http://www.webcitation.org/6mezCtxhS).

## Introduction

Essential tremor is a hyperkinetic movement disorder characterized by a postural and kinetic tremor commonly affecting the upper extremities, but the voice, head, and lower extremities can also be involved [1]. Symptoms can result in profound disability and social withdrawal due to embarrassment affecting the quality of life [2]. In the stage of medically refractory essential tremor, deep brain stimulation (DBS) is an approved and safe procedure to achieve tremor reduction [3]. The historical target of DBS and stereotactic lesioning in essential tremor is the thalamic ventral intermediate nucleus (Vim) [4,5]. Pre–magnetic resonance imaging (MRI)–era localization of this structure was based on anterior commissure–posterior commissure (AC-PC) coordinates, and intraoperative DBS electrode placement relied on intraoperative electrophysiological analysis and tremor testing with multiple parallel trajectories in the awake patient to achieve satisfactory tremor control. Although the Vim is precisely identifiable with custom MRI nowadays, image-assisted DBS electrode placement in the Vim is still performed with a combination of the above mentioned indirect targeting procedures [6,7]. This can be attributed to the fact that the stimulation of fiber tracts seems to be more effective than stimulation of subcortical nuclei like the Vim [8], and indeed best results in tremor suppression are achieved with stimulation in the subthalamic region rather than in the Vim [9]. Recent diffusion tensor MR imaging (DTI) tractography studies revealed that the dentatorubrothalamic tract (DRT) is a promising target structure in the subthalamic region, as the current coverage of DRT fibers in Vim-DBS results in satisfactory tremor control [10-12]. DTI tractography-assisted stereotactic surgery targeting the DRT would therefore not rely on multiple parallel trajectories and intraoperative tremor testing in the awake patient. Moreover, DBS implantation in general anesthesia would offer more patient comfort and a shorter duration of surgery, reducing associated risks (eg, infection) [13]. The abandonment of multiple parallel trajectories and successive electrode manipulation during intraoperative testing should reduce the risk of intracerebral hemorrhage [14]. In a retrospective analysis, Chen et al [15] found that DBS for essential tremor with classical AC-PC coordinate-based targeting of the Vim can be performed in general anesthesia safely and effectively.

This clinical pilot trial, Deep Brain Stimulation for Tremor Tractographic Versus Traditional (DISTINCT), in patients with medically refractory essential tremor aims at demonstrating safety of DTI tractography-assisted stereotactic surgery in general anesthesia and proving its equality compared to conventional AC-PC coordinate-based stereotactic surgery with intraoperative testing in the awake patient. Accordingly, a randomized, controlled, rater-blinded, parallel group study was set up involving 2 patient groups each assigned to 1 of the aforementioned treatments. Established assessments of tremor and quality of life are used to compare the effect of treatments, which is then related to effective electrode contact positions.

## Methods

### Design

This is an investigator-initiated monocentric, randomized, controlled, 2-armed, interventional, observer-blinded feasibility trial conducted at the Department of Stereotactic and Functional Neurosurgery and the Department of Neurology at the Freiburg University Medical Center.

The primary objective is to compare DBS-mediated tremor reduction for 2 different approaches—DTI tractography-assisted stereotactic surgery with target point of the DRT in general anesthesia and stereotactic surgery of the thalamic/subthalamic region as conventionally used—in patients suffering from essential tremor.

Primary outcome parameter will be the reduction of tremor as assessed with the Fahn-Tolosa-Marin Tremor Rating Scale (FTMTRS) [16] including blinded video rating.

### Secondary Objectives

To assess the effect in tremor reduction of both interventions at 6 months based on the total power in tremor analysisTo assess the quality of lifeTo assess the optimal electrode contact positionTo assess differences in duration of neurosurgery in both groupsPsychiatric assessmentTo assess safety of interventionTo show equality of both interventions in tremor reduction at 6 months based on the total power in tremor analysis

### Participants and Recruitment

We plan to recruit 24 male or female patients (12 per treatment group). Patients who are referred to our departments due to disabling medically resistant essential tremor are informed about this study. Patients who give their informed consent are registered in the trial and undergo the screening. Patients who gave their informed consent but do not undergo stereotactic surgery are regarded as screening failures. See Textbox 1 for eligibility criteria.

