#### Baseline

Baseline visit will be performed on the day prior to neurosurgery and includes assessment of tremor-related medications, FTMTRS, and tremor analysis.

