#### Day of Neurosurgery

Patients will be randomized within 7 days prior to neurosurgery; the DBS system will be implanted according to the randomized treatment group.

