#### Analysis of Secondary Endpoints

Effective tremor reduction (FTMTRS score reduction by 50% is regarded as “response”) at 12 months after intervention will be analyzed in an exact logistic regression model. Tremor reduction measured by tremor analysis and calculation of total power before and 6 and 12 months after intervention will be analyzed the same way as the primary endpoint.

Quality of life will be measured with the SF-36. The 8 summary scales per measurement will be evaluated based on the method implemented in the software program (SAS version 9.2 or higher, SAS Institute Inc) provided along with the questionnaire. Change from baseline will be evaluated for all summary scales after 6 and 12 months as the primary endpoint. BDI, effective contact position (with respect to DRT and AC-PC coordinates) and the volume of activated tissue will be analyzed similar to the primary endpoint using linear regression.

Rates of recruitment per month, screening failures, and drop-out from the trial will be evaluated and considered for the confirmative trial. All secondary analyses will be exploratory.

Safety analyses will be performed for all patients for whom 1 of the treatments was started. Patients will be analyzed according to treatment received. Rates of adverse events and serious adverse events will be calculated with corresponding 2-sided 95% confidence intervals.

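### Screening failure is defined by not having surgery, but randomization comes before surgery, so a randomized patient who is never operated on falls under two unreconciled rules

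*Protocol article*

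**What the plan says.** Four statements in the protocol article bear on this point.

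- **Participants and Recruitment:** "Patients who gave their informed consent but do not undergo stereotactic surgery are regarded as screening failures". The criterion is surgery. The sentence has no limit to the time before randomization.
- **Day of Neurosurgery:** "Patients will be randomized within 7 days prior to neurosurgery". There can thus be up to a week between allocation and operation.
- **Analysis of the Primary Endpoint:** the primary analysis follows intention to treat, and patients stay in their randomized arm "irrespective of whether they refused or discontinued the treatment or whether other protocol violations are revealed".
- **Analysis of Secondary Endpoints:** "Rates of recruitment per month, screening failures, and drop-out from the trial will be evaluated and considered for the confirmative trial". Screening failures and drop-outs are therefore two separate feasibility results.

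Two further statements give context. The Discussion explains that blinding patients was rejected, "so a rater-blinded design is implemented". The Baseline section adds: "Baseline visit will be performed on the day prior to neurosurgery", so that visit can fall after randomization.

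**The concern.** Screening normally ends at randomization, and a screening failure is someone who never reached it. Here the label extends to the operating room. A patient who is randomized and then withdraws before any stereotactic surgery fits the recruitment definition of a screening failure, and also fits the ITT description of a randomized patient who refused treatment.

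Two things are at stake.

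1. **The feasibility rates.** Withdrawal after allocation says something about how acceptable awake or asleep surgery is. It belongs in the drop-out rate, by arm. Counted as screening failure, it leaves the drop-out rate and is no longer attributed to an arm.
2. **The primary comparison.** A team that applies the label in its usual sense may stop following these patients or leave them out. That would be an exclusion after randomization. Patients are not blinded, and one arm is operated on awake with intraoperative testing while the other is under general anesthesia, so the exclusion could depend on the arm.

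**Working it through.** **Is there a figure to reproduce?** None for this point: the article gives no rate of non-operation after randomization. The only attrition figure is the 25% under Sample Size Calculation, where 24 × 1.25 = 30 gives the stated number to be assessed for eligibility. It is not split by arm or into before and after randomization, so it cannot size this problem.

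**The rules side by side.**

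| Patient | Participants and Recruitment | Analysis of the Primary Endpoint |
|---|---|---|
| Consented, not randomized, no surgery | Screening failure | Not in ITT |
| Randomized, no stereotactic surgery | Screening failure | In ITT, in assigned arm |
| Randomized, has the other arm's operation | Not a screening failure | In ITT, in assigned arm |
| Randomized, operated as assigned | Not a screening failure | In ITT, in assigned arm |

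Only the second row conflicts. Crossovers are not affected.

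**Can the second row occur?** Yes, because randomization may precede surgery by up to 7 days. If each of 24 randomized patients had probability p of no surgery (assumed), the chance of at least one such case is 1 − (1 − p)^24:

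- p = 2%: 38%
- p = 5%: 71%
- p = 10%: 92%

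**Effect on the feasibility rates (illustration).** Assume that all 30 assessed patients consent, 24 are randomized, 2 of these are not operated on, and there are no other drop-outs.

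- Defined by randomization: screening failures (30 − 24)/30 = 20.0%; drop-outs 2/24 = 8.3%.
- Defined by surgery: screening failures (6 + 2)/30 = 26.7%; drop-outs 0/22 = 0%.

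**Effect on an arm mean if such patients are excluded.** Each patient is 1/12 = 8.3% of an arm. Suppose 2 of 12 in one arm are excluded and would have scored 1 SD worse.

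- Worse than the mean of the other 10: shift = 2 × 1/12 = 0.17 SD.
- Worse than the whole-arm mean: shift = 2 × 1/10 = 0.20 SD.

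In terms of improvement, if k of 12 are unoperated and unchanged while the rest improve by r (both assumed), the arm mean is r × (12 − k)/12 and the gap to the mean after exclusion is r × k/12. This runs from 50% × 1/12 = 4.2 points to 70% × 2/12 = 11.7 points.

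**Effect on precision.** The 95% CI half-width for the difference in means is t(0.975; n1 + n2 − 2) × √(1/n1 + 1/n2), in SD units. It is 0.847 for 12 v 12, 0.868 for 11 v 12 and 0.893 for 10 v 12.

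**Do the data exist to honor ITT?** The Follow-Up section times the 6- and 12-month visits from neurosurgery, so an unoperated patient has no dated outcome visit. The day-before-surgery baseline visit may also be missed, although the FTMTRS is rated at screening too.

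**The case against.** The strongest reply is that the analysis section already has the right rule. The screening-failure sentence stands in a recruitment paragraph, directly after the mention of screening, and may be only a loosely worded flow label. The specific rule on who is analyzed would then govern. Much of this stands. A reader might infer that randomized patients who refuse are dropped from the ITT population, but no section says that screening failures leave any analysis set, and the section that defines the set says the opposite. What the article supports is a conflict between two rules, not a stated exclusion.

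A reader might also infer that anyone who refuses the assigned arm is affected. That is too broad: a patient who has the other operation has undergone stereotactic surgery and is outside the label.

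Arm-dependent refusal is possible but not shown. The article gives no refusal rate and does not say when, within the 7 days, patients learn their allocation. They have a disabling, treatment-resistant tremor and have consented to the trial.

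Finally, the gap of 4 to 12 percentage points arises only if unoperated patients have a 6-month FTMTRS or are imputed at no change. Without a score, they add nothing to a complete-case regression under either label. How missing scores are handled may be set out in a document not shown.

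The reply does not remove the conflict. Both rules are written down, so this is not detail left out of a condensed article. A SAP that keeps all randomized patients would still disagree with the recruitment sentence, and the overlap between the two feasibility rates would remain.

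**Conclusion.** The point holds as an unreconciled definition. A randomized patient without stereotactic surgery is a screening failure under Participants and Recruitment and an ITT patient under Analysis of the Primary Endpoint. Applied literally, the first rule distorts the screening-failure and drop-out rates meant for the confirmatory trial, and it could lead to an exclusion after randomization that may depend on the arm.

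The size cannot be determined from the article. The shift of 0.17 to 0.20 SD assumes that 2 of 12 patients in one arm are excluded, none in the other, and that they would have scored 1 SD worse. There may be few such patients, or none.

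This should be fixed, but it does not invalidate the primary analysis: the trial is an exploratory 24-patient pilot and its ITT rule is already sound.

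**What to change.** - In Participants and Recruitment, define the term by randomization: patients who consent but are not randomized are regarded as screening failures.
- Add that randomized patients without surgery remain in the ITT population and are counted as drop-outs, reported by arm.
- Where such a patient agrees, seek the FTMTRS at 6 and 12 months. Time these assessments from randomization or from the planned surgery date, because the current visits are timed from surgery.

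No sample size changes. The cost is a short protocol correction and an occasional extra follow-up visit. The first two changes resolve the conflict; the third gives the ITT analysis the data it needs for these patients.
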